### Data analysis

2.7.

#### Qualitative aspects

2.7.1.

All interviews will be voice recorded and transcribed with F4 verbatim. Subsequently, we will subject the entire interview material to qualitative content analysis using MAXQDA 2022. Following Mayring and Fenzl (96), we will combine, explicate, and structure the qualitative data with a main focus on building categories and systems of categories. In accordance with the working model of Mayring, we will focus on reducing, highlighting and verifying representative categories always in line with the entire output material (97). We will first assign interview passages into categories developed within the interview material in an inductive manner and proceed with analyzing and interconnecting the same codes in different sections of the interview (96). To meet qualitative standards of validity and objectivity, we will proceeed with two working steps. To assure intracoder validity, the analysis will be performed by the seond author (LS) in two isolated steps and the results will be converged afterwards (97). Furthermore, a second person (first author) will analyze the entire interview, with the research team subsequently discussing critical interview passages as well as disparities in the results (98).

#### Quantitative analysis

2.7.2.

The *pilot study* using a non-controlled pre-post design will be analyzed with paired sample tests. In this case, the time (pretest vs. posttest) will be treated as the independent variable and the PL domains as the dependent variables. Depending on the support or rejection of normal distribution (based on Kolmogorov Smirnov test), we will compute paired sample *t* tests or Wilcoxon tests for the inferential statistical comparison.

Furthermore, the Transparent Reporting of Evaluation with Non-Randomized Designs (TREND) statement will serve as an overarching framework (99) to guide the design, evaluation, and reporting of the *main study*. We will use a variance analytical design with multivariate character to quantitatively examine the effectiveness of the intervention arm in comparison to the control arm (repeated MANOVA). Statistically, main attention will be paid to the time-group interaction in the repeated MANOVA (within-subjects factor: time; between-subjects factor: group condition). We will determine the magnitude of the intervention effect on the eta square (*η*^2^) coefficient by adhering to the interpretation guidelines as suggested by Cohen (100). Despite the nested structure of data (e.g., classes as clusters), multilevel analysis (i.e., linear mixed methods) cannot be realized owing to the low number of second-order units (*N* ≤ 10 schools). Even robust methods, like the Kenward-Roger correction, require a larger number of clusters for adequate calculations (101). To account for potential clustering at the class level, we will enter the class as covariate within the MANOVA. Missing data in the longitudinal data set will be imputed with the expectation maximization (EM) algorithm (102). Nevertheless, we will withdraw children from the analysis who did not attend (a) the first session with the baseline measurement and (b) at least eleven of the 14 sessions (<75%; i.e., exclusion of those who were missing more than three sessions of the PL intervention).

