### Research questions, goals, and hypotheses

1.3.

The main goal of the present study is to investigate the effectiveness of a PL intervention in different schools in the city and city state of Bremen, Germany. This study addresses the following primary research question: *Can an intervention with clear foundations in the integrated PL domains systematically promote PL among children 8–11 years of age?* Accordingly, we will test the main hypothesis (one-sided procedure) that children in the intervention condition develop significantly better over the interventional period in PL outcomes compared to children in the control condition.

In addition, the present study pursues two sub-goals on its way toward the primary goal: (a) to derive holistic, age-specific intervention components for 8–11 years old children with explicit manifestations in the PL concept, and (b) to implement the intervention in cooperation with primary schools in the city and city state of Bremen, Germany. In case of a successful implementation and evaluation (i.e., approval of the research question), the present study also reserves capacities for potentially preparing the dissemination of the intervention concept.

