### Quantitative instruments

2.5.

In line with the theoretical five-domain structure applied by this study, we will choose a multidimensional assessment strategy to cover the different domains of PL. Due to acceptable measurement characteristics, the second version of the Canadian Assessment of Physical Literacy (CAPL-2) (84, 85), the Canadian Passport for Life (PFL) (86), or the Canadian Physical Literacy Assessment for Youth (PLAY) (87) were taken into account (88), all measuring the cognitive, psychological/affective, and physical domains of PL. As another alternative, the Physical Literacy in Children Questionnaire (PL-C Quest) will be selected as an opportunity for evaluation (89). Based on the Australian understanding of PL, the PL-C Quest is a picture-based self-assessment of the physical, psychological (affective), cognitive, and social domains. Available data from factor analyses indicate a good model fit for boys in the English-speaking setting (90). In detail, the psychometric properties of the procedure are reported as moderate (social domain) to good (physical domain), with model fit being better for boys than for girls. Additionally, the image-based method can be beneficial for children with language or comprehension difficulties. In the present study, we will consistently draw on the “summer items” (e.g., skateboarding instead of skating and safe swimming in the sea instead of safe tobogganing on the slopes) of the available item pool of the PL C Quest. A more detailed overview is given in Table 2.

**Table 2 T2:** A detailed overview of the quantitative assessments in regard to the PL domains.

	Physical domain	Cognitive domain	Psychological (affective) domain	Social domain	Behavioral domain
Pilot study 1 [uncontrolled pre-post design]	PL-C Quest [12 items]	PL-C Quest [7 items] CAPL-2 [5 items]	PL-C Quest [7 items] CAPL-2 [12 items]	PL-C Quest [4 items]	CAPL-2 [1 item]
Pilot study 2 [uncontrolled pre-post design]	PL-C Quest [12 items]	PL-C Quest [7 items] PFL [3 items] PLAYself [2 items]	CAPL-2 [6 items] PL-C Quest[7 items]	PL-C Quest [4 items]	CAPL-2 [1 item]
Main study [controlled design]	DMT 6–18 [8 tests] PL-C Quest [12 items]	Selection based on data from the pilot studies	Selection based on data from the pilot studies	PL-C Quest [4 items]	CAPL-2 [1 item]

CAPL-2, Canadian assessment of physical literacy, second version; DMT, Deutscher Motoriktest; PFL, passport for life; PL-C Quest, physical literacy in children questionnaire.

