### Sample size

2.6.

We performed sample size calculations with the software G*Power version 3.1 (94). For the uncontrolled *pilot study* adopting a pre-post character, we expect a minimum effect size of *d_z_* = 0.40 while considering the influence of general development effects. In this case, the minimum sample size to be acquired through one-sided, paired sample *t* tests (statistical power ≥ 80% and one-sided *p* < .05) will be *n* = 41. Assuming a conservative dropout rate of 25% (as usual for this target group, see (14, 95), an initial sample of *n* = 55 children will be recruited. Given an average number of approximately 20 pupils per class, we will include three to four classes for the pilot study.

For the subsequent main study in a control group design, we base a significant effect on time-group interactions of repeated multivariate analyses of variance (MANOVA). Aiming to control for general development effects through the involvement of a control arm, we set a smaller effect size of *d* = 0.30 (corresponding to *f* = 0.15) in this part of the study. Power calculations with an adjusted significance level (five PL outcomes:.05/5) of *p* ≤ .01 resulted in a required sample size of *n* = 134 children across the two study conditions (autoregressive pre-post correlation *r_t_* = 0.50, statistical power ≥ 80%). A total of nine to ten classes (dropout corrected *n* = 179 children) should initially participate in the main study.

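### The hypothesis is one-sided and the sample size fits single-outcome tests at 0.01, but the only test named for the main study is an omnibus MANOVA interaction, which gives neither direction nor domain and does not assure 80% power

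*Protocol article*

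**What the plan says.** Three sections of the protocol article define the main-study test.

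- **Section 1.3 (hypothesis):** "we will test the main hypothesis (one-sided procedure) that children in the intervention condition develop significantly better over the interventional period in PL outcomes", compared with control.
- **Section 2.6 (sample size):** "we base a significant effect on time-group interactions of repeated multivariate analyses of variance (MANOVA"). The same paragraph continues: "Power calculations with an adjusted significance level (five PL outcomes:.05/5) of *p* ≤ .01", giving 134 children, or 179 after dropout. No sidedness is given for this calculation, whereas the pilot calculation in the same section is explicitly one-sided.
- **Section 2.7.2 (analysis):** "main attention will be paid to the time-group interaction in the repeated MANOVA". The effect is to be sized by eta-squared. The section names no single-outcome test, significance level or direction.

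On the number of outcomes, the abstract and section 2.6 count five. The main-study row of Table 2 (section 2.5) lists two instruments for the physical domain, "DMT 6–18 [8 tests] PL-C Quest [12 items]". Section 2.5.1 presents the motor test as an addition to the self-report. The cognitive and affective measures are deferred to the pilot results.

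**The concern.** A multivariate interaction F and its eta-squared carry no sign. A significant result says that the vector of mean changes differs between arms. It does not say in which domain, or which arm did better. The hypothesis is that intervention children do better, and the abstract says that the results will decide on scale-up, so both pieces of information are needed.

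The alpha split points to a different test. One omnibus test yields one p-value and needs no division by five; dividing by five implies five separate tests, which section 2.7.2 does not name. If the sample size was computed for those tests, the stated 80% power does not carry over to the omnibus test.

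The five-way split also needs exactly one score per domain, and the physical domain has two candidates.

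**Working it through.** **Inputs from section 2.6:** f = 0.15 (given there as equivalent to d = 0.30), pre-post correlation r = 0.50, two time points (m = 2), two groups, alpha = 0.05/5 = 0.01, power at least 80%, N = 134. The plan gives no between-domain correlation, so values of 0, 0.3 and 0.5 are assumed below. Like the plan's own calculation, all figures treat children as independent.

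**1. Reproducing the plan's figure.** For one outcome, the repeated-measures within-between interaction has noncentrality λ = f²·N·m/(1 − r) on F(1, N − 2).
- λ = 0.0225 × 134 × 2 / 0.50 = 12.06.
- Power at alpha 0.01 on F(1,132) is 0.803, and 134 is the smallest N that reaches 80%.
- Dropout: 134/0.75 = 178.7, rounded up to 179, using the 25% stated for the pilot.

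So 134 is a correct answer for a single-outcome, non-directional test.

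**2. The one-sided version of that test.** In change-score terms λ = (N/4)·δ², so δ = √(4 × 12.06/134) = 0.6 SD of change. The one-sided t test at 0.01 has noncentrality 0.6 × √134 / 2 = 3.47. It needs N = 116, and its power at 134 is 0.867. Hence 134 does not correspond to the one-sided procedure of section 1.3.

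**3. The omnibus test of section 2.7.2.** With two time points, the multivariate interaction is Hotelling's T² on five change scores: F(5, 128) with λ = (N/4)·δ′Σ⁻¹δ, where N/4 = 33.5. Suppose one domain shifts by 0.6 SD and four do not. With equal correlation ρ, δ′Σ⁻¹δ = 0.36 × [1 − ρ/(1 + 4ρ)]/(1 − ρ).

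| Assumed ρ | δ′Σ⁻¹δ | λ | Power at 0.01 |
|---|---|---|---|
| 0 | 0.360 | 12.06 | 0.52 |
| 0.3 | 0.444 | 14.88 | 0.65 |
| 0.5 | 0.600 | 20.10 | 0.83 |

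The stated 80% is reached only at the highest of these correlations.

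**4. Direction.** λ is unchanged if δ is replaced by −δ. With all five domains shifted by 0.6 SD, ρ = 0.3 and alpha 0.05, δ′Σ⁻¹δ = 5 × 0.36/(1 + 4 × 0.3) = 0.818 and power is 98.9%, whether all five improve or all five worsen.

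**5. Number of scores.** Two physical scores plus at least one in each of four other domains makes at least six. At 0.01 each, the family-wise bound is 6 × 0.01 = 0.06 (1 − 0.99⁶ = 0.0585 if independent). A six-way split, 0.05/6 = 0.00833, would need N = 140, and power at 134 would be 0.785.

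**The case against.** The strongest defence is that section 2.6 already points to five domain-level tests. It speaks of interactions and analyses in the plural, divides alpha by five, and gives an N that matches the single-outcome test exactly. Direction can then be read from the group means. Rejection in the favourable direction would carry at most 5 × 0.005 = 0.025 error over five two-sided tests at 0.01, which supports a directional claim conservatively. Follow-up tests after a MANOVA may also sit in an analysis plan that is not shown.

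Much of this stands, and it is the reason for the fix proposed. It does not remove the conflict, because section 2.7.2 makes the omnibus interaction the main test and names no other. Reading direction from the means works for one outcome, but not for a single multivariate p-value when domains move in different directions.

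On the count of scores, the text consistently speaks of five outcomes, and a composite physical score would restore five. None is defined, but the excess error is small (6% against 5%).

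A reader might go further in three ways that the documents do not support:

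- **That 134 is miscalculated.** It reproduces exactly for a single-outcome F test.
- **That the omnibus test generally detects a uniform benefit less often than a mixed pattern.** Take five gains of 0.3 SD against two gains and two losses of 0.3 SD, at alpha 0.05. Power is 47% against 90% at correlation 0.3, but 85% against 75% at correlation 0. The ranking depends on an assumed correlation, and 0.3 SD of change is half the design effect.
- **That the eight motor tests each count as an outcome.** The article does not say that they will be analysed singly.

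**Conclusion.** The point holds as an inconsistency between three stated parts of the plan. Section 1.3 is directional, section 2.6 is sized for a non-directional test on one outcome at 0.01, and section 2.7.2 names an omnibus test. Followed as written, a significant result would not identify the domain or the favoured arm. Power for a change in one domain would lie between 0.52 and 0.83 over assumed correlations of 0 to 0.5. The lack of direction does not depend on any assumption; the power range depends on the correlations and on the plan's own effect size.

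It would be too strong to infer that the trial cannot support a claim of benefit. The same data analysed by domain can, and the planned N suffices for that under the plan's own inputs. The two-measure issue in the physical domain is minor. The matter should be settled before main-study data are seen.

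**What to change.** In section 2.7.2, make the confirmatory analysis five domain-level group-by-time (difference-in-change) contrasts.

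- **One score per domain.** Name it in advance. For the physical domain, choose between the motor test, the self-report and a defined composite before main-study data are seen. Fix the cognitive and affective scores once the pilots are evaluated, as already planned.
- **Sidedness.** State it in line with section 1.3. One-sided tests at 0.01 give power 0.867 at n = 134, with favourable-direction error of at most 5 × 0.01 = 0.05. Two-sided tests at 0.01 give 0.803 and hold that error at 0.025.
- **Multiplicity.** Use Bonferroni or Holm at overall 0.05; the first Holm step is the plan's 0.01.
- **Reporting and claims.** Report signed differences with confidence intervals for all five domains. Claim benefit only for the domains that pass, and report any worsening elsewhere alongside. A rule of overall success from one passing domain would not be enough, since it ignores losses in the others.
- **MANOVA.** Keep the omnibus test and eta-squared as supportive.

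This changes wording only, with the same data and the same N. The cost is that, unless a composite is defined, one physical measure becomes secondary.

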**Methods:**

The physical literacy intervention cultivates explicit theory-content links and comprises 12 heterogeneous sessions (each 60-90 min in length). The study contains three different phases with two initial pilot studies and a subsequent main study. The two pilot studies take a mixed-methods character by drawing on quantitative pre-post-designs as well as interviews with children (in groups). In the main study, we will longitudinally compare the course of PL values (five outcome domains: physical, affective, cognitive, social, behavioral) between two study arms: school classes of children are either assigned to an intervention condition (regular physical education and health care plus PL intervention) or to a control condition (regular physical education and health care only).

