### Dissemination aspects of this study

3.3.

In case of a successful main study with results justifying a further use of the PL intervention, the development of a dissemination strategy may come into play. Indeed, the present project has reserved personal, temporal, and financial resources for four months to potentially prepare a dissemination strategy that may flow into a follow-up study. For instance, teachers could be systematically trained for more sustainable, internal delivery in participating schools, potentially paralleled by an entire whole school approach permeating the entire institution (107, 108). A dissemination could also aim at reaching a wider target group by performing a so-called “scale-up” of the intervention (103, 104). Of course, the type of the scale-up depends on the results and their interpretations but also on pragmatic arguments and the development of the scholarly landscape on PL. For instance, a scale-up on the *geographical level* would implicate that also locations outside the city state of Bremen, Germany, could be addressed to reach children in other areas. Adopting the character of a *sectorial scale-up*, the successful intervention could be adapted and used in other settings, such as sport clubs or community-based work. As a further alternative, a scale-up on the *ontogenetic/chronological level* could mean that individuals of another age could benefit from a similar or slightly adapted PL intervention. In any case, dissemination strategies should also test whether the adapted PL intervention then also works in other settings, in other regions, or in individuals of another age.

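### The only stated measure of effect size, eta squared read by Cohen's guidelines, is biased upward and unsigned, and it cannot show whether the planned effect was reached

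*Protocol article*

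**What the plan says.** All references are to the protocol article.

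- **Section 2.7.2 (Quantitative analysis):** for the main study, "main attention will be paid to the time-group interaction in the repeated MANOVA". The size of the intervention effect is taken from eta squared, "by adhering to the interpretation guidelines as suggested by Cohen (100". No other magnitude measure is stated for the main study. The text does not say whether the coefficient is multivariate or per outcome, and it gives no numerical bounds.
- **Abstract (Methods):** there are "five outcome domains: physical, affective, cognitive, social, behavioral".
- **Section 1.3:** "we will test the main hypothesis (one-sided procedure"), so the claim has a direction.
- **Section 2.6 (Sample size):** "we set a smaller effect size of" d = 0.30, equated with f = 0.15. The pre-post correlation is 0.50, power is at least 80% and n = 134 (179 after dropout). The level is split: "Power calculations with an adjusted significance level (five PL outcomes:.05/5").
- **Section 3.3:** dissemination is considered "In case of a successful main study with results justifying a further use of the PL intervention". No threshold for eta squared is given there.

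**The concern.** Sample eta squared is a proportion of variance and cannot be negative, so chance differences between arms always push it above zero. The push grows with the number of outcomes pooled into one coefficient. Reading the raw value against fixed labels can therefore give an effect label to noise. Section 2.7.2 does not make the label depend on a significant test. The coefficient also looks the same whichever arm did better.

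The study was planned around a stated standardised effect, and readers will want to know whether the programme reached it. If the reported measure is not on the scale of the planned effect, they cannot tell.

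**Working it through.** **1. Reproduce the planned size.** Inputs from section 2.6: f = 0.15, two arms, m = 2 time points, r = 0.50, alpha = 0.01. For a within-between interaction with 1 and N − 2 degrees of freedom, the noncentrality is f² × N × m/(1 − r).

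- At N = 134: 0.0225 × 134 × 2/0.5 = 12.06, power 0.803.
- At N = 132: power 0.796.
- The minimum is 134, as stated, and 134/0.75 = 178.7, rounded up to 179, as stated.

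This is a one-degree-of-freedom, single-outcome calculation.

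**2. Multivariate eta squared under no effect.** For two groups and p change scores, eta squared (1 − Wilks' lambda) follows Beta(p/2, (N − 1 − p)/2), with mean p/(N − 1). Children are treated as independent. With p = 5 and N = 134 this is Beta(2.5, 64), with mean 5/133 = 0.038. The bounds below are assumptions, because the protocol gives none.

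| Condition | Null trials above the bound |
|---|---|
| N = 134, bound 0.01 | 93.5% |
| N = 134, bound 0.0196 (f² = 0.02) | 76.7% |
| N = 134, bound 0.06 | 15.6% |
| N = 134, bound 0.01, class using 8 df | 94.3% |
| N = 179 (no dropout), bound 0.01 | 88.2% |

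A simulation of 20,000 trials gave 93.6% for the first row at outcome correlations of 0, 0.3 and 0.5.

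**3. Per-outcome eta squared under no effect.** With p = 1 and N = 134 the mean is 1/133 = 0.0075, and 25.0% of null trials exceed 0.01 in a given domain (18.3% at N = 179). At least one of five domains exceeds it in 1 − (1 − 0.250)^5 = 76% if the domains are independent, and in 67% if they correlate 0.5.

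**4. What a significant result is called** (assumed bounds 0.01/0.06/0.14, N = 134).

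- Multivariate, alpha 0.05: critical F(5,128) = 2.285, so eta squared is at least 5 × 2.285/(5 × 2.285 + 128) = 0.082.
- Multivariate, alpha 0.01: critical F = 3.164, giving 0.110.
- Per outcome, alpha 0.01: critical F(1,132) = 6.83, giving 6.83/(6.83 + 132) = 0.049.

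A significant multivariate result is thus never 'small'. A significant per-outcome result can be.

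**5. The planned effect on the eta-squared scale.**

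- Direct conversion: f²/(1 + f²) = 0.0225/1.0225 = 0.022.
- From the calculation in step 1: 12.06/(12.06 + 134) = 0.083. The matching difference in change is √(4 × 12.06/134) = √0.36 = 0.60 change-score SDs. With r = 0.50 and equal SDs at both times, the change-score SD is √(2 × 0.5) = 1 baseline SD, so this is also 0.60 baseline SDs.

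On the assumed bounds the same planned effect is 'small' by one route and 'medium' by the other.

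**6. Dependence on outcome correlation.** If every domain has the same difference δ in change-score SDs and the domains correlate ρ, then D² = 5δ²/(1 + 4ρ), and population multivariate eta squared is (D²/4)/(1 + D²/4).

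| δ | ρ = 0 | ρ = 0.3 | ρ = 0.5 |
|---|---|---|---|
| 0.30 | 0.101 | 0.049 | 0.036 |
| 0.60 | 0.310 | 0.170 | 0.130 |

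The δ values are illustrative. The same per-domain effect gives quite different coefficients.

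**The case against.** The strongest reply is that eta squared with Cohen's guidelines is a conventional descriptive summary placed beside a significance test, and that the choice of coefficient, bounds and intervals can be left to an analysis plan. Under no effect, only about 5% of trials would be both significant on the multivariate test at 0.05 and labelled. This largely stands as a limit on the harm, and the absence of numerical bounds is not itself a fault. It does not remove the point. The article states a positive rule, the rule is the only magnitude measure given for the main study, and the label is not tied to significance.

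A reader might infer four stronger things that the document does not support:

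- **That 93% is a property of the plan.** It needs the multivariate coefficient and a 0.01 bound. The MANOVA wording favours the multivariate reading, but the .05/5 level and the single-outcome sample size point to per-outcome effects, where the rate is 25% per domain.
- **That a significant result can never be 'small'.** This holds only for the multivariate coefficient on the assumed bounds.
- **That the null mean of 0.038 exceeds the effect the study was planned for.** It exceeds 0.022, but not the 0.083 implied by the calculation behind n = 134.
- **That the label decides scale-up.** Section 1.3 links dissemination to confirming the research question, and section 3.3 refers to results and pragmatic arguments. Neither names eta squared.

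**Conclusion.** The concern holds in a conditional form. On either reading the stated measure is biased upward and cannot show direction for a directional hypothesis. At N = 134, chance alone passes an assumed 0.01 bound in about 93% of trials for the five-outcome coefficient (77% for a bound of 0.0196) and in about 25% per domain for the per-outcome one. Across the readings and sample sizes checked, the range is about 18% to 94%. These rates assume independent children; class clustering that the covariate does not remove would raise them.

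The mismatch with the planned effect does not depend on which coefficient is meant. The same f = 0.15 is 0.022 or 0.083 according to scale, so a Cohen label cannot show whether the planned effect was reached. This is a weakness in how magnitude is reported. It does not affect the validity of the significance test, and the document does not make the label a criterion for scaling up. The change should be made, because it is cheap and the present rule can mislead.

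**What to change.** In section 2.7.2, make the main magnitude measure, for each PL domain, the signed between-arm difference in pre-post change divided by the pooled baseline SD, with a 95% confidence interval. In section 2.6, state the scale on which the planned effect is defined (0.30 or 0.60 SDs of difference in change) before any comparison with it.

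If a variance-explained figure is kept for the MANOVA, say which one it is, use a bias-corrected version such as multivariate omega squared or epsilon squared with an interval, and do not apply Cohen's univariate labels to the multivariate coefficient.

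The cost is about a sentence in each section and a little more reporting, with no new data. The reported effect sizes will look smaller.

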**Figure 1 F1:**
[figure not shown]
Study design.

After the completion of the two pilot studies, we will follow up with the main study. The main study will more rigorously examine the effectiveness of the final PL intervention in a controlled design. In each school, an even number of classes of one grade level will participate in the study. Half of the classes will be assigned to the intervention condition, which will pass regular half-year education in primary school plus a weekly PL intervention. In contrast, the other half of the classes will be assigned to the control condition, which will undergo only regular half-year education in primary school without the additional PL intervention (see Figure 1). Randomization cannot be fully realized as pragmatic reasons co-influence the assignment to the different intervention arms (57). The main study, which also includes two measurement time points (e.g., pre and post), will take place between September 2023 and February 2024. In summary, the research design with two pilot cycles (51) accounts for potential pitfalls (e.g., revision of PL content) toward a sound examination of the effectiveness of the PL intervention. The final reporting of study will adhere to the recent physical literacy interventions reporting template suggesting a total of 14 items (58). The ethics committee of the University of Oldenburg, Germany, has approved the conduction of the study (sign Drs.EK/2022/057).

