The focus of the PL interventions will be placed on pupils of the third or fourth grade, wherein the class will serve as the level for the assignment to study conditions. Accordingly, the present study will address children aged between 8 and 11 years within the trial and analyses. Furthermore, children and their legal guardians will have to provide informed consent to study participation. In line with the inclusive potential of PL (69), children with diagnosed special needs will be invited to join the intervention (as long as they can participate in regular physical education) and evaluation. Nevertheless, they will be excluded from the analysis for psychometric reasons.

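### Entering class as a MANOVA covariate does not protect the time-by-group test against clustering, because whole classes are assigned to one condition

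*Protocol article*

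**What the plan says.** Section 2.2 (Setting, participants, and recruitment) makes the class the unit of assignment: "the class will serve as the level for the assignment to study conditions". Section 2.1 (Study design) adds "In each school, an even number of classes of one grade level will participate in the study" and "Half of the classes will be assigned to the intervention condition". Section 2.6 (Sample size) plans "A total of nine to ten classes" for the main study and assumes about 20 pupils per class.

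Section 2.7.2 (Quantitative analysis) bases the evaluation on the time-by-group interaction of a repeated MANOVA. It acknowledges that the data are nested but states that multilevel analysis "cannot be realized owing to the low number of second-order units (*N* ≤ 10 schools"), and it also sets aside the Kenward-Roger correction for lack of clusters. In their place it offers: "To account for potential clustering at the class level, we will enter the class as covariate within the MANOVA". It does not say whether class is to be a categorical factor or a numeric code.

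**The concern.** No class contains children from both conditions, so class is nested in condition. Adjusting for a nested unit cannot work as adjusting for an ordinary covariate does. Either class carries all the information about condition, or it enters in a form too weak to represent the correlation among classmates.

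This is the confirmatory test of the main hypothesis, and the abstract says that the results will decide whether the intervention is scaled up. If children's changes are correlated within class, a child-level test treats about 134 children as independent when nine or ten classes were assigned. Its standard error is then too small, and the adjusted 1% level per domain is not kept.

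**Working it through.** **1. The plan's own figure.** Section 2.6 gives f = 0.15, pre-post correlation 0.50, alpha 0.05/5 = 0.01, power 80% and two groups at two times. The within-between interaction formula is λ = f² · N · m / (1 − r), with m = 2 times and df (1, N − 2). At N = 134, λ = 0.0225 × 134 × 2 / 0.50 = 12.06 and power is 0.803. Dropout of 25% gives 134 / 0.75 = 179. Both stated figures reproduce. Nothing in the formula allows for clustering.

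**2. The effect on the change scale.** With two time points, the time-by-group test is the group comparison of change scores, for which λ = (N/4) · δ². Hence δ = 2 · √(12.06 / 134) = 0.60 SD of change.

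**3. Class as a factor.** For ten classes the design has an intercept, condition and nine class indicators: 11 columns, rank 10. Condition is an exact linear combination of the class indicators. Once time-by-class is in the model, time-by-group has no unique estimate.

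**4. Class in any other form.** Simulation under no effect used change scores with SD 1, ten classes of 13 (134 / 10 ≈ 13), five per arm, and a two-sided nominal level of 1%. The ICCs are assumptions. Ranges cover repeated runs and two ways of ordering the class codes.

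| ICC of change (assumed) | No class term | Numeric class code | t test on class-mean changes |
|---|---|---|---|
| 0.02 | 1.9–2.3% | 2.0–2.3% | 0.9–1.1% |
| 0.05 | 3.9–4.3% | 4.0–4.4% | 0.9–1.1% |
| 0.10 | 8.2–8.6% | 8.3–8.9% | 0.9–1.1% |

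A class term not crossed with time does not enter the change-score comparison, so it behaves as the "no class term" column. Class effects nested in condition, contrasted against within-class error, give 4.3–4.7% at ICC 0.05 and 9.7–10.0% at ICC 0.10.

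A hand check agrees. The naive standard error is too small by about √(1 + 12 · ICC), which is 1.11, 1.26 and 1.48. The critical value of 2.61 then acts as 2.35, 2.07 and 1.76, with two-sided normal tails of about 1.9%, 3.9% and 7.8%.

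**5. Power of the class-level test.** The variance of a class mean is ICC + (1 − ICC)/13. The standard error of the arm difference is √(variance × 2/5). The critical t on 8 df at two-sided 1% is 3.36. For δ = 0.60:

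| ICC | Standard error | Noncentrality | Power |
|---|---|---|---|
| 0 | 0.175 | 3.42 | 56% |
| 0.02 | 0.195 | 3.07 | 45% |
| 0.05 | 0.222 | 2.70 | 34% |
| 0.10 | 0.260 | 2.31 | 23% |

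**The case against.** The strongest reply is that the authors saw the nesting, had too few clusters for a mixed model and chose a pragmatic adjustment. The first two parts stand. Few clusters are a real difficulty, and the source cited against Kenward-Roger is not available here to dispute. But few clusters call for a class-level or small-sample method. They do not make a class covariate a substitute for one.

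Several stronger readings are tempting and are not supported:

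- *The primary test cannot be computed at all.* That holds only for class as a factor crossed with time, and the coding is not stated. Even with nested class effects, a contrast of their averages can be computed. Its defect is the error term.
- *The reference to ten schools contradicts the design.* With an even number of classes per school, ten classes come from at most five schools. But the text gives an upper bound, which five satisfies. It is a wrong-unit slip: the assigned clusters are classes.
- *The covariate will destroy power.* If class codes ran 1–5 in one arm and 6–10 in the other, the correlation with condition would be 0.87 and the variance inflation factor 1/(1 − 0.87²) ≈ 4.1. This is a worst case only. Classes are split within schools, and nothing suggests codes ordered by arm.

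It is also fair to object that the class-level test is not exactly 1% in every setting. If change also varies between schools, the unpaired version is conservative, at about 0.2–0.5%.

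**Conclusion.** The concern holds in this form: no reading of class as a covariate corrects the time-by-group test for clustering of change. The nesting follows from the plan's own assignment rule and is not an assumption.

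The size of the error is conditional. At a nominal 1% it is about 2%, 4% and 8.5% for ICCs of change of 0.02, 0.05 and 0.10, with equal classes of 13. It vanishes only if that ICC is essentially zero. That 134 reproduces is no rebuttal, since the formula treats children as independent.

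The calculations use a two-sided 1% level, as the formula behind 134 does, although section 1.3 words the hypothesis as one-sided. The point concerns standard errors only. The non-random assignment, which the limitations section acknowledges, is a separate matter.

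**What to change.** - Drop class as a covariate.
- Make the primary analysis, for each domain, a comparison between conditions of class-mean pre-post changes, using t on (classes − 2) degrees of freedom at the planned 1% level. It needs no mixed model, so it is compatible with the plan's reservation about Kenward-Roger. Note that it is conservative if change varies between schools.
- Keep the child-level repeated MANOVA as descriptive.
- Name classes, not schools, as the clusters.
- Do not substitute a permutation of class labels within schools. Two classes in each of five schools give 2⁵ = 32 arrangements, so the smallest one-sided p is 1/32 = 0.031, which cannot reach 0.01.

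The analysis change costs wording and code and needs no new data. The cost in power is substantial and should be stated. With ten classes, power for the 0.60 SD change effect is about 56%, 45%, 34% and 23% at ICCs of 0, 0.02, 0.05 and 0.10. Section 2.6 should therefore restate its 80% claim, with the assumed ICC given.
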